#### Sample size estimation

The Swedish Childhood Cancer Registry has some 9880 Swedish persons diagnosed when 0–18 years registered since 1982. However, some will have been classified as having a benign tumour, some have been registered twice and some will be deceased. As such, the number of potentially eligible cases will be lower and estimated to be approximately 5745. Sample size calculation indicated that a minimum of 365 participants would be required, with a power of 0.9 and p<0.05 (two-tailed). Assuming a response rate of approximately 40%, as indicated by a systematic review of participation rates in self-administered questionnaire studies with childhood cancer survivors,^69^ we estimate inviting 913 potential participants to achieve the required sample size.

### Procedure

#### Online survey

Potential participants accessing the survey via the U-CARE-portal will be presented with study information in both text and video format. Participants will not be offered any financial reimbursements for taking part in the survey. Those interested will be able to log into the U-CARE portal using a study log-in code and will need to identify themselves via mobile telephone and/or Bank ID (a citizen authentication system). Potential participants will then be able to provide informed consent online and will be presented with brief screening questions asking for: (1) date of birth; (2) age when diagnosed with cancer; (3) date of last cancer treatment completed; (4) able to read and write in Swedish (yes/no); and (5) whether currently residing in Sweden (yes/no). Eligible participants will be provided access to the online survey (see ‘Survey items’ section). The online survey will be open for a period of 6 weeks. Each item completed in the survey is auto-saved and participants are able to select ‘save and continue later’ if they wish to return to the survey before submitting. On completion of the survey, a purposive sample of participants with past and/or present experience of mental health difficulties will be invited to take part in an interview (see ‘Embedded qualitative interview study’ section for further details). These participants will be provided with study information and online consent form, as well as asked to provide contact details.

#### Paper-based survey

Potential participants receiving study invitation via mail-out will be able to complete a paper-based survey. The survey includes a written consent form and brief screening questions as the online survey. Participants can return the paper-based survey to the study team using the freepost envelope provided in the study invitation pack. In addition, participants will be asked to provide consent if they agree to be contacted about participation in an interview study.

#### Reminders

Reminder study invitation packs will be resent at 2 and 6 weeks after sending the initial study invitation to AYACCS who do respond to the study invitation. It will be clearly stated in the study information sheet that reminder letters will be sent to non-responders. In addition, participants who consent to complete the online survey will receive reminders via SMS and email to complete the survey at 4 weeks, 2 weeks and 2 days prior to the survey closing.

### Survey items

An online and paper-based survey, consisting of 98 items in Swedish. The survey comprises eight subsections: (1) sociodemographic characteristics (11 items); (2) clinical cancer-related characteristics (3 items); (3) actual help-seeking behaviour (2 items); (4) attitudes towards internet-administered interventions (17 items); (5) stigma of mental illness (5 items); (6) MHL (26 items); (7) social support (12 items); and (8) current symptoms of depression, anxiety and stress (21 items). One open question at the end of the survey offers and opportunity to provide any further information concerning emotional distress and preferences for support after childhood cancer. Potential predisposing, enabling, environmental, and need-related factors examined with the survey are summarised in table 1.

**Table 1 T1:** Factors to be examined as per Andersen’s behavioural model of health services use

Andersen’s behavioural model of health services use	Factors*
Predisposing	Sex (male/female/other) Age (16–24/25–39) Time since first cancer treatment (years) Place of birth (born in Sweden/born outside of Sweden) Childhood negative events (yes/no) Level of education (≤upper secondary school/>upper secondary school) Public stigma (Stigma Scale for Receiving Psychological Help) Mental health literacy
Enabling	Type of cancer (leukaemia/central nervous system tumour/solid tumour/lymphoma/other) Relationship status Employment status (yes/no/studying) Social support (12-item Interpersonal Support Evaluation List)
Need-related	Symptoms of depression (DASS-21 depression subscale) Symptoms of anxiety (DASS-21 anxiety subscale) Symptoms of stress (DASS-21 stress subscale) Self-reported experience of mental health difficulties in past 6 months (yes/no)
Environmental	Region of Sweden (south/mid/north) Rural or urban area
Actual help-seeking behaviour (dependent variable)	Receipt of mental health support in the past 6 months Type of mental health support received in the past 6 months (formal/technology/informal)

*Outcomes selected informed by previous research.^32 42 50 70^

DASS-21, Depression Anxiety and Stress Scale.

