
### Data analysis

#### Statistical analysis

All statistical analyses will be conducted using SPSS V.26.0 software (IBM SPSS Statistics for Windows, 2019, Armonk, New York, USA). Sociodemographic and clinical characteristics will be presented with descriptive statistics. The potential association between predicting factors as informed by Andersen’s behavioural model of health services use (predisposing, enabling, environmental, and need-related factors) and the dependent variable help-seeking behaviour, for example, receipt of mental health support in the past 6 months will be examined using univariable and multivariable logistic regressions.^70^ The non-help-seeking group will used as the reference group.^70^ First, univariable analyses will be conducted for each predictor separately. Variance inflation factor will be used to examine multicollinearity prior to the regression analysis. A multivariable logistic regression will be performed using stepwise manual backward selection procedure. All predictor variables will initially be included, and non-significant predictors will be eliminated with only variables significantly related to the dependent variable (p<0.05) retained. For both the univariable and multivariable logistic regressions, ORs will be presented, alongside 95% CIs, and p values. Given the heterogeneous nature of the study population, subgroup analysis will be performed by stratifying the population by age and sex. The same method of modelling will be used for the subgroup analyses for age (15–19 years vs 20–29 years vs 30–39 years) and sex (male vs female). The subgroup analysis will be exploratory and with results used to inform subsequent studies.

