Despite the strengths of this study, the design presents some limitations. First, only those AYACCS who report receiving mental health support in the past 6 months are defined as help-seeking. However, this approach may lead to the exclusion of AYACCS who have attempted to seek formal help but not accessed. Second, the cross-sectional design does not allow us to draw any conclusions regarding cause and effect. Third, the study does not offer any compensation to participants. Research suggests compensation can facilitate the recruitment of minority populations and those from lower socioeconomic backgrounds.^93^ Subsequently, this may limit the representativeness of the sample and generalisability of results, especially to marginalised young adults who may already be at an elevated risk of not seeking mental health support.^94^ Forth, the current study includes a broad age range (16–39 years) and it may be expected that adolescents will have differing needs and preferences to young adults in their 20s or 30s. Indeed, a common limitation of research in the area is the inclusion of heterogeneous samples across different age groups.^95^ However, the study is designed to be a first step towards developing more acceptable and relevant interventions for the population and may inform future research with specific AYACCS subgroups, taking into account a number of sociodemographic and clinical factors (eg, gender, current age, age at diagnosis, and cancer type). Fifth, the length of the survey may lead to respondent fatigue (eg, lower levels of attention and motivation in later sections of the questionnaire), potentially resulting in poorer quality data or missing data. Finally, we will not evaluate response bias via comparisons of respondents versus non-responders for mailed surveys.

In conclusion, results of the study may have the potential to improve access to tailored, relevant, and acceptable mental health support for this currently underserved population.

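### Age enters the main logistic models only as 16–24 versus 25–39 although date of birth is collected; if help-seeking changes gradually with age, information is lost and the leftover age effect loads on time since first treatment.

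*Protocol article*

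**What the plan says.** Under Survey items, Table 1 fixes the coding of the predisposing factors: "Age (16–24/25–39) Time since first cancer treatment (years"). Age has two classes; time since first treatment is in years.

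Under Procedure, Online survey, respondents meet "brief screening questions asking for: (1) date of birth; (2) age when diagnosed with cancer". The Paper-based survey section says the paper form carries the same screening questions, so exact age can be computed for every respondent.

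Under Statistical analysis, each predictor is tested alone and then a multivariable model is built: "All predictor variables will initially be included, and non-significant predictors will be eliminated", with p<0.05 as the criterion for staying in. Age-stratified models in three bands (15–19, 20–29, 30–39) are planned as exploratory.

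The 16–24/25–39 cut also appears under Recruitment, as a balancing factor when invitation blocks are drawn from the registry. The Discussion says of the broad age range that "it may be expected that adolescents will have differing needs and preferences to young adults in their 20s or 30s".

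**The concern.** The first research question asks which factors, age among them, are associated with help-seeking. A 15-year upper band treats a 25-year-old and a 39-year-old as the same person for adjustment. Balancing the invitations on two bands does not require the same cut in the model, and the article gives no reason for a cut at 25.

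The pairing matters more than the banding alone. Time since first treatment is roughly current age minus age at first treatment. The screening items listed are age at diagnosis and date of last treatment, so the variable would probably be derived from age itself. With a coarse age factor beside a fine-grained relative of age, age variation inside the bands can be credited to time since treatment. A real age gradient would then be more easily missed or eliminated, and a survivorship factor with no effect of its own more easily retained and reported. The three-band subgroup models do not alter the adjustment in the main model.

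**Working it through.** **The plan's own figures.** The invitation number reproduces: 365 / 0.40 = 912.5, rounded up to 913. The 365 cannot be recomputed, because the Sample size estimation section gives no predictor, odds ratio or help-seeking rate. It fits several designs. One is a binary predictor split 50/50 with odds ratio 2.0 and a reference rate of 50%, which needs 364.

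**Information kept by the two bands.** Assume the log-odds are linear in age. A two-class version then keeps a share r² of the information, where r is the correlation between age and the indicator for 25 or over. With integer ages uniform within each band, the band means are 20 and 32 and the within-band variances 6.67 and 18.67. Then r = 12 × √(p(1−p)) / SD(age), with p the share aged 25–39.

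| Assumed age mix | p | SD(age) | r | r² | 365 × r² |
|---|---|---|---|---|---|
| Uniform 16–39 | 0.625 | 6.92 | 0.839 | 0.70 | 257 |
| Bands equally filled | 0.50 | 6.98 | 0.860 | 0.74 | 270 |
| 25% aged 16–24 | 0.75 | 6.53 | 0.795 | 0.63 | 231 |

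As an illustration of scale, take an age effect for which age in years would have univariable power 0.90. Power with bands is Φ((1.960 + 1.282) × r − 1.960), that is 0.78, 0.80 and 0.73.

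**Leftover age effect.** Simulation assumptions: n = 365, ages uniform over 16–39, age at diagnosis uniform over 0–18, 25% help-seekers, only age and time in the model, and no true effect of time. Under this type of assumption time correlates about 0.79 with age overall, and 0.44 and 0.64 within the younger and older band.

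| True age OR per 10 years | False positives for time, bands | False positives for time, years | Time retained after backward elimination, bands | Time retained after backward elimination, years |
|---|---|---|---|---|
| 0.8 | 6% | 5% | 13% | 12% |
| 0.7 | 9% | 5% | 22% | 16% |
| 0.6 | 13% | 4–5% | 34% | 18% |
| 0.5 | 20% | 4–5% | 38% | 13% |

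With no age effect, both codings give about 5% in the full model. Joint-model power for age rises from 25% (bands) to 41% (years) at OR 0.6, and from 42% to 67% at OR 0.5.

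**Scale of these effects.** Ages 16 and 39 are 2.3 decades apart, so the four odds ratios imply 0.8^2.3 = 0.60, 0.7^2.3 = 0.44, 0.6^2.3 = 0.31 and 0.5^2.3 = 0.20 between the youngest and oldest respondents.

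**The opposite shape.** With a true step at 25 (OR 0.5), univariable power is 0.81 with bands and 0.67 with linear age, and joint-model power is 57% against 33%. The full-model false-positive rate for time stays at about 5–6% with bands.

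**The case against.** A reader might infer that the two bands leave age below the power the protocol promises. The document does not support that. It says "a minimum of 365 participants would be required, with a power of 0.9 and p<0.05 (two-tailed") and names no predictor. For the binary predictor described in the working, two-band age would have 0.9 by design. The loss can only be stated relative to age in years.

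The shape of the age effect is also unknown, and a step at 25 would favour the bands. The Discussion sentence contrasts adolescents with adults in their 20s or 30s. That is a group difference and does not establish a gradient within 25–39. Only fairly strong gradients produce a large distortion; at OR 0.8 per 10 years the two codings hardly differ.

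Nor does age in years cure everything. A quadratic or 3-knot spline tests age on two degrees of freedom, and at the noncentrality giving 0.90 on one degree of freedom (3.242² = 10.51) that yields 0.835. Backward elimination would still wrongly retain time in more than 5% of samples. The plan also checks variance inflation, fits exploratory age strata and disclaims causal inference.

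All of this stands and limits the size of the point. It does not justify the cut: exact age is in hand, no reason is given for expecting a change at 25, and under a gradual effect age in years does better on every measure computed.

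**Conclusion.** The point holds as a conditional loss of efficiency and a conditional misattribution. If help-seeking changes gradually with age, the two-band coding discards about 26–37% of the age information. It also raises the full-model false-positive rate for time since treatment from about 5% to between 6% and 20%, over age odds ratios of 0.8 to 0.5 per 10 years. The age mix, the help-seeking share, the distribution of age at diagnosis, the linear shape and the two-variable model are assumptions; the article gives none of them. If the effect were a step at 25, the bands would lose nothing. The protocol's 0.9 is not contradicted. Because the data are already collected and the change is small, it is worth making.

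**What to change.** In Table 1, replace the two age classes with age in years, computed from date of birth. In the Statistical analysis section, state that age enters the univariable and multivariable logistic models as a continuous term, with a pre-specified check for non-linearity (a quadratic or 3-knot restricted cubic spline term). Keep 16–24/25–39 for drawing invitation blocks and for descriptive tables.

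Cost: one table entry and one sentence, with no new data. The odds ratio is read per 10 years instead of as a two-group contrast. A non-linear term uses one extra degree of freedom and part of the power gain. Power is lower than with bands if the true effect is a step at 25. Backward elimination may still retain time since treatment wrongly more than 5% of the time, so its result should be read together with the full model.

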#### Actual help-seeking behaviour

The following items will be used to examine actual help-seeking behaviour: (1) emotional health difficulties related to the childhood cancer experience; (2) the type of support received by those who accessed support in the past 6 months and/or in the past (not including the past 6 months): (a) face-to-face individual or group support from mental health professional; (b) face-to-face support from a general practitioner/family doctor; (c) technology-administered mental health support (eg, online therapy programme, smartphone application, video conferencing or teleconferencing); (d) technology-administered support from a general practitioner/family doctor (eg, online, video conferencing or teleconferencing); (e) social media support group; (f) phone help-line; (g) family, partner or friend/s; (h) religious leader; and (i) other. Type of support will be categorised into: (1) face-to-face professional support; (2) technology-administered professional support; and (3) informal support (social media support group, family, partner, friends and religious leader). Those who sought support for mental health difficulties in the past 6 months and received support from a health professional either face-to-face or technology assisted will be defined as ‘help-seeking’.^70^

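### Mental health difficulties in the past 6 months are tested as a predictor of an outcome that already presupposes them, so the odds ratio is largely definitional and may not be estimable

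*Protocol article*

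**What the plan says.** Three parts of the protocol article bear on this.

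- **Predictor.** Table 1 (Survey items) puts "Self-reported experience of mental health difficulties in past 6 months (yes/no") among the need-related factors, next to the three DASS-21 subscales.
- **Outcome.** The section on actual help-seeking behaviour classes as help-seeking "Those who sought support for mental health difficulties in the past 6 months and received support from a health professional", whether face to face or by technology. Table 1 gives the dependent variable as "Receipt of mental health support in the past 6 months", and the statistical analysis section refers to "help-seeking behaviour, for example, receipt of mental health support in the past 6 months". Neither of these two states a difficulties condition or requires a professional source. The limitations list and the Discussion also describe the outcome as receipt of support.
- **Model.** On the comparison group the analysis section says: "The non-help-seeking group will used as the reference group". It does not restrict the analysis to respondents with difficulties. All predictors enter first, then "non-significant predictors will be eliminated with only variables significantly related to the dependent variable (p<0.05) retained". The test behind the p value is not named. ORs, 95% CIs and p values are promised for the univariable and multivariable models, and the same modelling is repeated in three age groups and two sexes.

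The help-seeking block has two items. One asks about "emotional health difficulties related to the childhood cancer experience", with no time window in the description. The other records "the type of support received by those who accessed support in the past 6 months" or earlier.

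**The concern.** Predictor and outcome share a construct and a time window. If a person can be a help-seeker only by seeking support for difficulties in the past 6 months, someone who reports none in that period is a non-help-seeker by construction, yet still counts in the reference group. The association is then built in for that half of the table.

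Two poor results can follow for the first research question. The item may be reported as the leading factor associated with help-seeking when the link is mainly definitional. Or it may be removed as unrelated because the maximum likelihood estimate does not exist. Removal would also change the other ORs, since the item is the only need measure tied to the outcome window.

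**Working it through.** **Inputs.** From the document: n=365 (Sample size estimation) and the p<0.05 retention rule. The plan gives no expected OR or prevalence for this item, so there is no figure of its own to reproduce. Assumed: 30-60% report difficulties; 30-50% of those are help-seekers; 0, 1 or 3 help-seekers answer no to difficulties (discordant respondents below).

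**Formulas.** Let a and b be help-seekers and non-help-seekers with difficulties, and c and d the same without. Then OR = ad/(bc), and SE(log OR) = sqrt(1/a + 1/b + 1/c + 1/d). The likelihood-ratio (LR) chi-square is twice the log-likelihood gain over the intercept-only model.

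**Strict definition, c = 0.** The OR has a zero denominator, so no finite OR or CI exists. Twenty Newton iterations stop at an OR of 6.9e8 to 1.6e9 with SE about 2,520 to 3,330. These are stopping points, not estimates. Wald p is 0.993-0.995. The LR chi-square stays well defined. For 60% with difficulties and 30% helped (a=66, b=153, d=146), the log-likelihoods are about -134.0 and -172.5, giving 77.0 (p=1.7e-18, the largest p in the grid).

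**Looser wording, c = 1 or 3.** Worked extremes:
- 30%/50%, c=1: 55 x 254 / (55 x 1) = 254
- 60%/30%, c=1: 66 x 145 / (153 x 1) = 62.5; SE = 1.01; Wald p = 4.5e-5
- 30%/50%, c=3: 55 x 252 / (55 x 3) = 84
- 60%/30%, c=3: 66 x 143 / (153 x 3) = 20.6; Wald p = 5.0e-7

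| Difficulties / helped | Helped among those with difficulties | LR chi-square, c=0 | OR, c=1 | OR, c=3 |
|---|---|---|---|---|
| 30% / 30% | 33 of 110 | 87.2 | 109 | 36.0 |
| 30% / 50% | 55 of 110 | 157.0 | 254 | 84.0 |
| 40% / 50% | 73 of 146 | 162.9 | 218 | 72.0 |
| 60% / 30% | 66 of 219 | 77.0 | 62.5 | 20.6 |
| 60% / 50% | 110 of 219 | 143.2 | 146 | 48.1 |

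**Backward elimination.** This was simulated with n=365, eight predictors and 200 runs per setting:

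| Help-seekers among respondents without difficulties | Runs with an empty cell | Item dropped, Wald | Item dropped, LR |
|---|---|---|---|
| 0% | 100% | 100% | 0% |
| 0.5% | 40% | 40% | 0% |
| 1% | 13.5% | 13.5% | 0% |
| 2% | 1% | 1% | 0% |
| 5% | 0% | 0% | 0% |

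The Wald drop rate matches the empty-cell rate in every setting.

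**Age strata.** Assume three equal groups of about 122, of whom 55% (67) report no difficulties. If 1% of those are help-seekers, a stratum's cell is empty with probability 0.99^67 = 0.51, and at least one of three is empty with probability 1 - 0.49^3 = 0.88. At 2% the figures are 0.98^67 = 0.26 and 1 - 0.74^3 = 0.59. In the full sample (201 without difficulties) they would be 0.99^201 = 0.13 and 0.98^201 = 0.02.

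**The case against.** The strongest reply is that the document does not establish an empty cell. Most descriptions of the outcome mention only receipt of support. Someone continuing therapy for an earlier problem could truthfully report no difficulties in the past 6 months. If the predictor comes from the help-seeking block's difficulties item, which concerns the cancer experience, a person helped for other distress could answer no and still be a help-seeker. Item wording and skip logic are not shown. This stands: a reader might infer that the OR must be infinite, and the document does not support that. One discordant respondent makes it finite and clearly significant.

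A reader might also infer that the elimination rule will delete the item. That needs both an empty cell and a Wald test. No test is named, an LR test keeps the item, and in a manual procedure an analyst would see a standard error near 3,000.

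Nor is the association a full tautology. Answering yes does not determine help-seeking, and need is one of the four components of the behavioural model the study uses. If the item went, the three DASS-21 subscales would still represent need.

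The looser wording does not rescue the plan, however. The sentence in the help-seeking section is the explicit classification rule, and its conflict with the other wordings leaves open whether the model can be estimated. An LR test settles retention but does not supply the OR and CI that the analysis section promises.

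**Conclusion.** The concern holds in limited form. The OR for this item is largely definitional, because the outcome includes seeking support for difficulties in the same 6 months and people without difficulties remain in the reference group.

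Under the strict definition there is no finite OR or CI, and Wald-based elimination would remove the strongest variable despite an LR chi-square of 77 to 163. Under the looser wording the item is kept with an OR of about 62-254 (one discordant respondent) or 21-84 (three), which should not be read as an independent association. Empty cells are more likely in the planned subgroup models than in the full sample.

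The sizes rest on the assumed prevalences and discordance counts. The overlap itself rests only on the document's wording.

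**What to change.** 1. State one outcome definition and use it in Table 1, the help-seeking section and the statistical analysis section. It should say whether a difficulties condition and a professional source are required.
2. Take this item out of the p<0.05 backward elimination and report it as a cross-tabulation with the outcome. Alternatively, fit the help-seeking model among respondents with difficulties.
3. If the item is kept as an adjustment, force it in, fit by Firth penalised likelihood, and do not interpret its OR as an independent association.
4. Base removal of other factors on the likelihood-ratio test, in the subgroup models too.

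**Cost.** Only wording changes; no new data are needed. One factor fewer is listed as a tested association. The DASS-21 subscales still cover need, though as current symptoms rather than over the 6-month window. Restricting the model would narrow the question to people with difficulties and leave about 110 to 219 of 365 respondents under the assumed 30-60%.
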